### Outcomes

The primary outcome is health-related quality of life associated with respiratory symptoms according to the CAT Scale [29] 4 weeks after starting the treatment. CAT is a validated scale to quantify and monitor the impact of COPD on well-being and daily life. It consists of 8 questions (rated from 0 to 5 points) and a total score of 0–40 (0–9 mild, 10–20 moderate, 21–30 severe, and 31–40 very severe). A difference of 2 or more points in health status is considered clinically significant [30].

The following are the secondary outcomes:
Exercise capacity will be measured as the number of repetitions performed in the 1-min sit-to-stand test (1MSTS) [31], which consists of sitting down and getting up from a chair with no hand support as many times as possible for 1 min while connected to a saturation monitor. Measurements include the number of repetitions and oxygen saturation before and after performing the exercise.The Post-COVID-19 Functional Status Scale (PCFS) [32] focuses on relevant aspects of daily life during post-infection follow-up. The scale is intended to help health professionals become aware of functional limitations and to determine the degree of disability.Severity of common symptoms of patients with long COVID will be evaluated using Likert scales [33] [0 (less severe) to 10 (most severe)]: asthenia, headache, mental confusion (brain fog), ageusia, and anosmia.Use of health services, counting number of visits: virtual, primary care center, emergency room, and hospital admissions.Mortality.Sick leave days at day 28 (end-of-treatment).Side effects of the drug occurring at any time of the study period will be assessed and recorded in the data collection platform eCRF.Treatment compliance (percentage of pills taken at the end of treatment) will be estimated at the end of treatment by counting the remaining pills in the bottle or, if not possible, by directly asking the patient.

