### Sample size

In the data published by Wang et al. [34] to evaluate an intervention in stable COPD patients, a weighted common standard deviation of the CAT score of 5.69 was observed. Basing the sample calculation on these data, in a study of the superiority of montelukast compared to placebo with an intention-to-treat analysis, accepting an alpha risk of 0.05 and a beta risk under 0.2 in a two-tailed contrast, 142 individuals in the treatment group and 142 in the control group are needed to detect a difference of 2 units. We assume a 10% loss to follow-up rate.

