### Randomization, allocation, implementation, and blinding process

Participants will be randomly allocated to the intervention (treatment) or control (placebo) group. The randomization will be carried out by a IDIAPJGol statistician not involved in the recruitment using the R statistical software to obtain computer-generated random numbers without stratification, in a 1:1 allocation ratio by blocks of 4. The distribution will be made by blocks to ensure the proportionality of treatments between centers.

The randomization list will be provided to the pharmacy, which will label the trial treatments accordingly. Each treatment will be identified with a unique code. The centers will have medication in sequential order. The medication code dispensed to the patient will be registered on the medication dispensing form and on the data collection logbook. Since this is a double-blind study, neither healthcare professionals, patients nor the research team will be aware of the allocated group. Montelukast pills and their placebo equivalent will be visually identical.

Unblinding of a participant’s treatment will be allowed when information of the treatment received is needed for the effective and secure management of the patient.

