#### Phone call (days 7, 21, and 56)

Health-related quality of life associated with respiratory symptoms, post-COVID-19 functional impairment, and symptom progression will be evaluated by means of a telephone call using the same questionnaires. Information regarding the number of visits to the health center, primary and/or hospital emergency care, and hospitalization since the previous visit will be assessed, as well as the use of concomitant medication, evaluation of adverse events, and compliance with study medication.

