### Statistical analysis

Baseline characteristics of the sample will be described for each group using mean and standard deviation for quantitative variables and absolute and relative frequencies for qualitative variables. Bivariate comparison of characteristics between patients taking montelukast and patients taking placebo will be carried out to verify group comparability. The Wilcoxon test will be used for the comparison of quantitative variables and the chi-square test for the comparison of qualitative variables (or the Fisher test in case of extreme distributions in the crossed tables). In all comparisons, the statistical significance will be set at 5%.

Outcome measures will be described and compared between the montelukast and placebo groups using the same statistics. No multivariate analysis will be performed.

For the primary endpoint analysis (montelukast efficacy) and secondary endpoints, we will primarily use an intention-to-treat analysis. We will also conduct a per-protocol analysis. R-4.0.2 for Windows will be used.

Additional subgroup analysis will be performed based on symptom duration (< 6 months and ≥ 6 months).

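### The primary comparison is an unadjusted Wilcoxon test at day 28 with modelling ruled out, so baseline and interim CAT scores go unused although about 10% of day-28 scores are expected to be missing

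*Protocol article*

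**What the plan says.** All references are to the protocol article.

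- **Outcomes** fixes one time point: "The primary outcome is health-related quality of life associated with respiratory symptoms according to the CAT Scale [29] 4 weeks after starting the treatment". The same section takes a difference of 2 or more CAT points as clinically significant.
- **Statistical analysis** names the Wilcoxon test for quantitative variables, applies the same statistics to the outcome measures, and says that no multivariate analysis will be done. It then sets the analysis population: "For the primary endpoint analysis (montelukast efficacy) and secondary endpoints, we will primarily use an intention-to-treat analysis". A per-protocol analysis is added.
- **Sample size** plans for missing scores: "We assume a 10% loss to follow-up rate".
- **Table 2** marks CAT at enrolment and at every visit from day 1 to day 56. For days 7, 21 and 56 the telephone section says that quality of life "will be evaluated by means of a telephone call using the same questionnaires".

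The article gives the baseline, day-7, day-14 and day-21 CAT scores no role in the primary comparison. It does not say what happens to a patient without a day-28 CAT; neither exclusion nor imputation is mentioned.

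**The concern.** Each statement is ordinary on its own, but together they fit poorly. A two-sample Wilcoxon test of day-28 CAT needs a day-28 score from each patient it counts. The sample size expects about one patient in ten to lack that score. The label says all patients are compared as randomized. Unless something is imputed, the label and the comparison describe different sets of patients.

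Two things are at stake. First, if dropout relates to response differently in the two arms, a comparison of completers is biased, and the interim scores that could largely correct this are not used. Second, even with harmless dropout, an unadjusted single-time-point test gives up the precision that baseline CAT offers. Both losses follow from the stated method, and the exclusion of modelling closes off the usual way of avoiding them.

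**Working it through.** **Inputs from the article.** Sample size gives the SD ("a weighted common standard deviation of the CAT score of 5.69 was observed"), the error rates ("accepting an alpha risk of 0.05 and a beta risk under 0.2 in a two-tailed contrast") and the target ("142 individuals in the treatment group and 142 in the control group are needed to detect a difference of 2 units"). Randomization is "in a 1:1 allocation ratio by blocks of 4".

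**Step 1: reproduce the sample size.**
n per arm = 2 × (z₀.₉₇₅ + z₀.₈₀)² × SD² / Δ² = 2 × (1.960 + 0.8416)² × 5.69² / 2² = 127.06.
With 10% loss: 127.06 / 0.9 = 141.2, rounded up to 142. Without inflation the figure would be 128, so the loss is already inside the 142.

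**Step 2: expected day-28 scores.**
0.9 × 142 = 127.8 per arm; 284 − 2 × 127.8 = 28.4, so about 28 patients without a score. At 127.8 per arm, power is 80.2% by the normal approximation. It is about 78.4% for a Wilcoxon test on normal data (relative efficiency 3/π). There is no slack.

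**Step 3: when completers mislead.** Let d be the fraction missing in an arm and g the mean day-28 CAT of the missing minus that of completers. The full-arm mean is the completer mean plus d × g, so the error in the treatment difference has size |d_M g_M − d_P g_P| (M montelukast, P placebo).

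- Same d and g in both arms: 0.
- d = 0.10 in both arms, g equal in size and opposite in sign: 2 × 0.10 × g, which is 0.4 for g = 2 and 0.8 for g = 4. For a full SD (g = 5.69) it is 1.14, an extreme case.

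**Step 4: simulation.** 142 per arm, SD 5.69, about 10% missing at day 28, dropout depending on the day-21 score, 3,000 runs per scenario. The between-visit correlation (0.5 and 0.7) is an assumption, because the article gives none. Size of the completer difference and Wilcoxon rejection rate:

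| Dropout | Correlation | True 0: difference | True 0: rejection | True 2: difference |
|---|---|---|---|---|
| Random | 0.5 | 0.00 | 5.6% | 1.99 |
| Random | 0.7 | 0.01 | 4.9% | 2.00 |
| Same mechanism in both arms | 0.5 | 0.02 | 4.6% | 2.02 |
| Same mechanism in both arms | 0.7 | 0.00 | 5.1% | 1.99 |
| Opposite by arm | 0.5 | 0.53 | 11.4% | 2.52 |
| Opposite by arm | 0.7 | 0.74 | 17.0% | 2.72 |

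In the opposite rows, worse patients leave montelukast and better patients leave placebo, so the error favours montelukast. Swapping the arms reverses the sign: a true 2 would then appear as about 2 − 0.52 = 1.48 or 2 − 0.72 = 1.28. An estimate using baseline and days 7, 14 and 21 under missing-at-random returned about 0 and 2 in every scenario. That is expected, because dropout was made to depend on an observed score.

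**Step 5: precision when dropout is harmless.** The unadjusted standard error is 5.69 × √(2/127.8) = 0.712. Adjusting for baseline with correlation r multiplies it by √(1 − r²): 0.866 at r = 0.5 and 0.714 at r = 0.7, reductions of 13% and 29%. If the interim scores also recovered everything lost to dropout, a further factor √0.9 = 0.949 would apply, giving 18% and 32%. The truth lies between, hence roughly 15 to 30%. Most of this gain comes from baseline CAT; the interim scores serve mainly as protection against bias.

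**The case against.** The strongest reply is that the article never prescribes a complete-case analysis. A reader might infer one from the Wilcoxon test and the 10% allowance, but inflating for loss is compatible with an imputed intention-to-treat analysis, and no sentence says that patients without a day-28 score are left out. A reader might also infer that excluding multivariate analysis removes every alternative. It does not: that sentence follows the one on between-group comparison, and a Wilcoxon test can be run on imputed day-28 scores, including scores imputed from days 7 to 21. Rules for missing data are commonly left to a full protocol or SAP, so their absence from an article is no finding. All of this stands.

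It also stands that the documents give no evidence of differential dropout. The bias scenario is deliberately unfavourable, its direction is undetermined, and response-related dropout does no harm when it works alike in both arms. A two-group test at one time point is a legitimate design choice, and the article gives the telephone calls another purpose, limiting memory bias. Finally, a mixed model restricted to patients with some post-baseline CAT also misses those lost before day 7.

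What the reply does not answer is the stated method itself. The article does more than stay silent: it names an unadjusted test and rules out modelling. A later SAP that made a repeated-measures model primary would contradict the published text.

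**Conclusion.** The point holds in a limited form and is worth acting on. The stated primary test uses neither baseline nor interim CAT. With about 28 of 284 day-28 scores expected to be missing, it is a complete-case comparison unless values are imputed, and the article does not reconcile that with its intention-to-treat label.

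The documents do not support saying that lost patients will be excluded, or that the result will be biased. Bias is about zero under random dropout or a common mechanism. It is about 0.5 to 0.7 points in either direction, with type I error of 11 to 17%, under opposite mechanisms with about 10% missing per arm. Against a 2-point target that would be material, but it rests on an assumed mechanism and on assumed correlations of 0.5 to 0.7. The precision argument needs only the correlations: a standard error lower by roughly 15 to 30%. Confidence is medium.

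**What to change.** 1. Lift the exclusion of multivariate analysis for the primary endpoint.
2. Take the day-28 contrast from a repeated-measures mixed model on CAT at days 7, 14, 21 and 28, with baseline CAT, visit, treatment and treatment-by-visit, including every randomized patient with any post-baseline CAT.
3. Keep the Wilcoxon test of day-28 CAT as a supportive analysis.
4. Add one delta-adjusted or reference-based sensitivity analysis that also covers patients with no post-baseline CAT, so that all randomized patients are represented.
5. State which patients enter each analysis, so that the intention-to-treat label matches the set analysed.

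Cost: wording and modest programming. Every CAT score needed is already scheduled, so no visits or patients are added. The downside is reliance on a missing-at-random assumption, which the sensitivity analysis probes, and on a model for mean differences, for which the Wilcoxon test offers a check.

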## Objectives

The main objective of this study is to evaluate the efficacy of 4 weeks of treatment with 10 mg/day of oral montelukast versus placebo in improving the health-related quality of life associated with mild to moderate respiratory symptoms in patients with long COVID as measured by the CAT questionnaire [29].

One of the secondary objectives is to evaluate the effect of montelukast versus placebo on improving the following: exercise capacity, COVID-19 symptoms (such as asthenia, headache, brain fog, ageusia, and anosmia), oxygen desaturation during exertion, functional status, mortality, use of healthcare resources, days of sick leave, and medication side effects. Additionally, we will evaluate antinuclear antibodies as markers of the response to montelukast.

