#### Inclusion visit (day 1)

Investigators will collect the following baseline information: sociodemographic data, clinical data, use of concomitant medication, health-related quality of life associated with respiratory symptoms, functional status post-COVID-19, and scoring of asthenia, headache, mental confusion, ageusia, and anosmia.

Participants will perform the 1MSTS test to evaluate the degree of dyspnea on exertion and oxygen desaturation.

A baseline blood test will be performed, including complete blood count, electrolytes, kidney function, liver function, C-reactive protein, creatine kinase, ferritin, d-dimer, type B natriuretic peptide, antinuclear antibodies, lupus anticoagulant, and quantitative anti-SARS-CoV-2 antibodies.

Patients will receive a bottle with the medication (montelukast or placebo), and an appointment for the next visit (on day 7) will be scheduled.

The patient will be asked to return the bottle with the study medication at the end of the study.

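### The symptom-duration subgroup has no stated comparison of the treatment effect between strata, and the ban on multivariate analysis shuts out the usual one

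*Protocol article*

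**What the plan says.** All references are to the protocol article.

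- **Statistical analysis.** Quantitative variables are compared by the Wilcoxon test and qualitative ones by chi-square or Fisher, with 5% significance for every comparison. Outcomes are compared between the arms with the same tests. That paragraph ends: "No multivariate analysis will be performed". The section's last sentence reads "Additional subgroup analysis will be performed based on symptom duration", split at 6 months. It names no method for comparing the two strata.
- **Objectives.** A further aim is stated: "we will evaluate antinuclear antibodies as markers of the response to montelukast". No analysis is given for it.
- **Inclusion visit (day 1).** "A baseline blood test will be performed", and antinuclear antibodies are on its list, so the marker is measured before treatment.
- **Sample size.** "142 individuals in the treatment group and 142 in the control group are needed to detect a difference of 2 units", with "a weighted common standard deviation of the CAT score of 5.69 was observed" as the SD source and "We assume a 10% loss to follow-up rate".
- **Symptom duration at entry.** The Participants text gives 4 to 12 weeks. Inclusion criterion b in Table 1 gives more than 4 weeks and less than 1 year.

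**The concern.** Whether montelukast works differently in shorter and longer illness is a question about the difference between two treatment effects. Testing montelukast against placebo separately in each stratum does not answer it. One significant and one non-significant result can easily arise when the effect is the same in both, because each stratum has only part of the trial's power. The standard remedy is a model with treatment, stratum and their product, and the ban on multivariate analysis would normally be taken to exclude it. An analysis plan that added such a model would contradict the protocol's wording, so this is a stated restriction and not merely a detail left for later.

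The stake is a conclusion that the drug helps patients with recent symptoms but not those with long-standing symptoms, or the reverse, resting on chance. The antibody aim has the same structure. A baseline marker of response to the drug must be judged by whether the treatment effect differs by marker status. Comparing outcomes by antibody status alone would mix prognosis with response to treatment.

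**Working it through.** **Inputs.** From Sample size: SD 5.69, difference 2 CAT points, two-sided alpha 0.05, power 0.80, 10% loss, 142 per arm. The split between duration strata is not in the documents, so 50/50 to 90/10 is assumed. Randomization is not stratified, and each stratum is taken to be balanced between arms.

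**Step 1: the plan's own figure.** n = 2 × (5.69 × (1.960 + 0.842) / 2)² = 127.06 per arm. Allowing for loss, 127.06 / 0.9 = 141.2, which rounds up to 142. The stated size reproduces. Evaluable patients: 142 × 0.9 = 127.8, taken as 128 per arm.

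**Step 2: power within a stratum.** With m per arm, SE = 5.69 × √(2/m) and power = Φ(2/SE − 1.96) + Φ(−2/SE − 1.96). At 50/50, m = 64, SE = 1.006, 2/SE = 1.988, and power is 0.511.

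**Step 3: chance that exactly one stratum is significant when the true effect is 2 points in both.** P = p1(1 − p2) + p2(1 − p1).

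| Assumed split | Power, larger stratum | Power, smaller stratum | Exactly one significant |
|---|---|---|---|
| 50/50 | 0.511 | 0.511 | 0.500 |
| 70/30 | 0.653 | 0.338 | 0.550 |
| 80/20 | 0.711 | 0.242 | 0.609 |
| 90/10 | 0.760 | 0.144 | 0.685 |

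**Step 4: sensitivity.**
- No effect in either stratum: 2 × 0.05 × 0.95 = 0.095.
- Uniform 1-point effect: 28% to 30% across the splits.
- Uniform 3-point effect: 26% to 72%.
- All 142 per arm evaluable, 2 points: 49% to 71%.
- Wilcoxon efficiency 3/π applied to m, 2 points: 0.500, 0.546 and 0.602 at 50/50, 70/30 and 80/20.
- Simulation with Wilcoxon tests on rounded CAT-like scores (4,000 runs, 128 per arm), 2 points: 50%, 55% and 60% at the same three splits.

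**Step 5: direct comparison of the two stratum effects.** With a common true effect the difference centres on zero, so the error rate is 5% by construction. The simulation gave 5.1% to 5.9%, with a true effect of 0 or 2 points. Its precision:
- 50/50: SE = 5.69 × √(2/64 + 2/64) = 5.69 × 0.25 = 1.42. The 95% half-width is 1.96 × 1.42 = 2.8 points. Power for a 2-point interaction is 29%. The interaction detectable with 80% power is 2.80 × 1.42 = 4.0 points.
- 80/20: SE = 1.78, half-width 1.96 × 1.78 = 3.5 points, power 20%, detectable interaction 5.0 points.

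**Step 6: antibodies.** The documents give neither a prevalence nor an analysis, so no error rate can be computed.

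**Step 7: can the subgroup exist?** Under the 4-to-12-week limit in the Participants text, nobody enters with 6 months of symptoms and the second stratum is empty. Under Table 1 both strata can fill.

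**The case against.** The best defence is that the subgroup gets one sentence in a condensed article, which names no wrong test, and that subgroup methods commonly belong in the analysis plan. The ban closes the paragraph on overall outcome comparisons, and the subgroup sentence comes later as an addition, so the ban may not be meant to reach it. This is fair as far as it goes. Silence alone would be no finding. What remains is that the section fixes bivariate arm comparisons at 5% for all comparisons and rules out the usual model without an exception. The scope of the ban therefore needs stating.

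Several stronger readings are tempting, and the documents do not support them:

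- *The plan bans all models and leaves only stratum tests.* It bans multivariate analysis. A z test of the difference between two stratum effects needs no multivariable model and stays open, though it is not named.
- *The trial would often report false differences.* No section says that discordant p-values will be read as effect modification. The 50% to 61% is how often discordance would occur under a uniform 2-point effect. With no effect it is about 10%.
- *The comparisons are within-group.* They are montelukast against placebo inside each stratum, not before-after changes within an arm.
- *The antibody analysis is wrong.* None is stated, so there is nothing to call wrong.

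It is also true that the interaction test has little power here. That argues for showing the interval and an exploratory label, not for separate p-values, which hide the imprecision.

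**Conclusion.** The point holds in limited form. The stated tools do not compare the treatment effect between duration strata, and the usual model for doing so is excluded on an ordinary reading. At the effect the trial is designed to detect, separate stratum tests would disagree in about 50% to 61% of trials for splits from 50/50 to 80/20, although the effect is the same in both. That discordance could be misread as effect modification. A direct comparison holds the error near 5%. These figures rest on SD 5.69, 128 evaluable per arm, a uniform 2-point effect and assumed splits.

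For antinuclear antibodies the conclusion is only about principle: an analysis of response to montelukast should compare treatment effects by antibody status. The primary comparison is not affected, so this is worth correcting but does not threaten the main result. Separately, the two statements of eligible symptom duration contradict each other, and one of them would empty a planned stratum.

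**What to change.** 1. State that the exclusion of multivariate analysis does not apply to effect modification. Report the difference between the two stratum effects on CAT (each a montelukast-placebo mean difference) with its 95% CI. Use a model with treatment, duration stratum and their product or, if the exclusion is kept, a z test of the difference between the two stratum effects. The plan contains no adjusted CAT model to which a term could simply be added, so the first option changes the stated approach and the second does not.
2. Show each stratum effect with its CI, make no significance claim for a single stratum, and label the analysis exploratory.
3. If antinuclear antibodies are analysed as markers of response, use the same form, with treatment effect by baseline antibody status, also exploratory.
4. Reconcile the symptom-duration limits in the Participants text and Table 1, so that it is clear whether the stratum of 6 months or more can contain patients.

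The cost is a few sentences in the protocol or analysis plan. No new data are needed, because symptom duration is checked at entry and the antibodies are in the baseline blood test. The downside is that the result will be visibly imprecise: a half-width of about 2.8 points at equal strata and about 29% power for a 2-point interaction.
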